## Methods

2

### Study Objective

2.1

#### Primary Objective

2.1.1

The primary objective of this study is to evaluate the effect of a patient‐centered education program on HIV virological outcomes among adults living with HIV‐HBV co‐infection. The corresponding primary outcome will be the change in plasma HIV RNA viral load, measured as log‐transformed HIV viral load (log_10_ copies/mL) from baseline to the end of the 6‐month follow‐up period. This outcome will be assessed using plasma HIV RNA viral load testing to quantify changes in virological response over time. In addition, HIV virological suppression, defined as a plasma HIV viral load of < 1000 copies/mL, will be evaluated as a secondary clinical outcome at the end of follow‐up.

#### Secondary Objectives

2.1.2

To assess the effect of the patient‐centered education intervention on medication adherence to ART and HBV‐active medications among adults living with HIV‐HBV co‐infection.

The corresponding secondary outcome will be medication adherence, measured using the context‐adapted Hill‐Bone Medication Adherence Scale (HBMAS) and analyzed using both continuous adherence scores and categorical adherence levels (good vs. poor adherence).

To evaluate changes in participants' knowledge and awareness regarding HIV following the patient‐centered education intervention.

The corresponding secondary outcome will be the HIV‐HBV‐related knowledge score, measured using a structured questionnaire and reported as a composite score, with higher scores indicating better knowledge and awareness.

To assess the effect of the patient‐centered education intervention on retention in HIV care among adults living with HIV‐HBV co‐infection.

The corresponding secondary outcome will be retention in care, measured by participants' attendance at scheduled clinic visits, continuity of follow‐up care, and adherence to routine clinical monitoring throughout the 6‐month study period.

#### Exploratory Objectives

2.1.3

To explore factors associated with HIV virological suppression among adults co‐infected with HIV and HBV, including sociodemographic, clinical, and behavioral characteristics.

To explore the relationship between changes in HIV‐HBV‐related knowledge, ART adherence, and HIV virological suppression following the intervention.

To assess the acceptability and feasibility of implementing the patient‐centered education program in routine HIV care settings.

### Research Question

2.2

This study seeks to address the following research questions: What is the effect of a patient‐centered education intervention on HIV virological outcomes among adults living with HIV in North‐West Ethiopia? To what extent does the intervention improve participants' knowledge of HIV‐HBV co‐infection, self‐management practices, medication adherence, and retention in care? In addition, the study will explore the individual, behavioral, clinical, and health system factors that may influence the implementation and effectiveness of the intervention. Furthermore, the study will assess the feasibility, acceptability, and potential integration of the patient‐centered education intervention into routine ART service delivery.

### Null Hypothesis

2.3

The null hypothesis of this pilot quasi‐experimental study states that the patient‐centered education intervention will have no statistically significant effect on HIV virological outcomes among adults living with HIV in North‐West Ethiopia compared with standard care. Specifically, it assumes that there will be no significant difference between the intervention and comparison groups in the change in HIV viral load over the study period. Furthermore, the intervention is hypothesized to produce no significant improvement in secondary outcomes, including medication adherence, self‐management practices, retention in care, and patient knowledge regarding HIV‐HBV co‐infection. In addition, the intervention is assumed to demonstrate no significant difference in feasibility, acceptability, or potential for integration into routine ART service delivery compared with standard practice.

### Alternate Hypothesis

2.4

The alternative hypothesis of this pilot quasi‐experimental study is that, compared with standard care, the patient‐centered education intervention will result in a statistically significant improvement in HIV virological outcomes among adults living with HIV in North‐West Ethiopia. Specifically, participants receiving the intervention are expected to demonstrate greater reductions in HIV viral load over the study period compared with those receiving standard care. Furthermore, the intervention is hypothesized to significantly improve secondary outcomes, including medication adherence, self‐management practices, retention in care, and patient knowledge regarding HIV‐HBV co‐infection. Additionally, the intervention is expected to be feasible, acceptable, and suitable for integration into routine ART service delivery, thereby demonstrating potential for broader implementation in similar healthcare settings.

### Trial Design

2.5

To assess the effect of a patient‐centered education intervention on HIV‐related clinical outcomes among adults living with HIV–HBV co‐infection in North‐West Ethiopia, this study will employ a pilot quasi‐experimental pre–post design with non‐randomized intervention and comparison groups. Participants receiving care at the comparison site will continue to receive routine standard HIV care, whereas participants at the intervention site will receive a structured patient‐centered education program integrated into routine ART services. The intervention effect will be evaluated by comparing changes in outcomes over time between the two groups using a difference‐in‐differences approach. The primary outcome will be assessed as a continuous measure, specifically the change in log‐transformed HIV viral load (virological response), while secondary outcomes will include medication adherence, self‐management practices, retention in care, and disease‐related knowledge. Outcome measurements will be collected at two time points: baseline (before intervention implementation) and endline (6 months after intervention initiation). Participant recruitment and baseline assessment will commence in December 2025, followed by intervention implementation and follow‐up from January to June 2026, with end‐line data collection completed in June 2026.

### Study Participant

2.6

#### Inclusion Criteria

2.6.1

Eligible participants will be adult people living with HIV aged 18 years or older who are receiving ART, have been on routine follow‐up for at least 6 months, have poor virological outcome (HIV viral load ≥ 1000 copies/mL), receive HIV care at the selected study sites, and are willing to participate in both baseline and endline assessments.

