#### Primary Outcome

2.10.1

HIV viral load will be measured at baseline and at the end of the 6‐month follow‐up period in both the intervention and comparison groups. The primary outcome will be assessed as the change in log‐transformed HIV viral load (log_10_ copies/mL) from baseline to endline, enabling quantification of the magnitude of virological response over time. The intervention effect will be evaluated by comparing the mean change in log‐transformed viral load between the intervention and comparison groups using a pre–post analytical framework.

In addition, virological suppression (VS) will be evaluated as an important clinical outcome and will be defined as an HIV viral load of < 1000 copies/mL, based on the most recent viral load measurement obtained within 30 days before or after the scheduled 6‐month follow‐up assessment. Assessments will be conducted at equivalent time points in both groups to ensure a comparable observation window. Data on viral load will be obtained from patient medical records and laboratory viral load testing reports.

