**Figure 1 hsr273167-fig-0001:**
[figure not shown]
The CONSORT flow diagram of participant allocation, follow up, and analysis of effect of patient‐centered education on HIV virological suppression among unsuppressed adult people living with HIV‐HBV co‐infection in North‐West Ethiopia (*n* = 120).

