Outcome assessments will be conducted at two time points: baseline and at the end of the 6‐month follow‐up period. Changes in primary and secondary outcomes including HIV virological outcomes, medication adherence, HIV‐HBV‐related knowledge, self‐management practices, and retention in care will be compared between the intervention and comparison groups to evaluate the effectiveness of the patient‐centered education intervention.

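### For the secondary suppression outcome, the entry criterion fixes baseline at 0% in both arms, so a difference-in-differences is only a crude endline contrast of two hospitals; adjust it for baseline log10 viral load

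*Protocol article*

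**What the plan says.** Section 2.6.1 (Inclusion Criteria) admits adults on ART who "have poor virological outcome (HIV viral load ≥ 1000 copies/mL". Section 2.10.1 (Primary Outcome) says that virological suppression "will be evaluated as an important clinical outcome and will be defined as an HIV viral load of < 1000 copies/mL"; sections 2.1.1, 2.12.4 and 2.13.1 use the same cut-off. The Figure 1 caption describes the study as one "among unsuppressed adult people living with" HIV-HBV co-infection.

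The primary outcome is something else. Section 2.5 (Trial Design) states: "The primary outcome will be assessed as a continuous measure", namely change in log10 viral load. Suppression, in section 2.1.1, "will be evaluated as a secondary clinical outcome at the end of" follow-up.

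Three general statements on analysis could reach suppression. Section 2.5: "The intervention effect will be evaluated by comparing changes in outcomes over time between the two groups", by difference-in-differences (DiD). Section 2.11.3 says that these will be compared between the groups: "Changes in primary and secondary outcomes including HIV virological outcomes". Section 2.15 (Data Analysis) fits a linear mixed model for each outcome, with the group-by-time interaction as the DiD estimate. Its covariate list has twelve entries, none of them baseline viral load. The Abstract has a different list that includes baseline viral load, for a multivariable linear regression. Section 2.8 assigns one hospital to each arm purposively.

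**The concern.** A DiD is meant to remove a difference that already exists between the groups before the intervention. It can do so only if the outcome is free to differ at baseline. Entry at or above 1000 and success below 1000 are exact complements, so suppression cannot differ at baseline and the subtraction does nothing.

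What can differ between the hospitals is the starting level above 1000, and that affects who crosses the line by 6 months. Dichotomising discards this information, and the section 2.15 covariates do not put it back. A hospital whose patients start nearer to 1000 would show more suppression without any effect of education, while the label DiD would suggest that baseline differences had been handled. The Discussion ties its case for putting patient-centered education into HIV-HBV treatment recommendations to improved viral suppression, so the reading of this secondary outcome matters.

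**Working it through.** **1. Algebra for suppression.** Let pI and pC be the proportions suppressed at 6 months. With the qualifying value as baseline, both baseline proportions are 0/60 = 0. Then DiD = (pI − 0) − (pC − 0) = pI − pC, the crude endline difference. A linear mixed model for this 0/1 outcome would also have no variance at baseline.

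**2. The same check for log10 viral load.** Baseline values vary above log10 1000 = 3.0, so the baseline means can differ and are subtracted. This DiD is not degenerate.

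**3. Size, first set of assumptions (none of these inputs is in the documents).** No intervention effect; baseline log10 viral load normal with SD 0.7, truncated at 3.0; 6-month change with mean −d and SD 1.0 in both arms. P(suppressed) is the average of Φ(3 − b + d) over the truncated baseline distribution of b.

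| Mean before truncation | Mean among enrolled | d = 0.5 | d = 1.0 |
|---|---|---|---|
| 3.6 | 3.84 | 38.6% | 56.1% |
| 4.0 | 4.11 | 30.4% | 46.7% |
| Difference | −0.27 | +8.2 points | +9.4 points |

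The change is the same in both arms, so the true log10 DiD is 0.

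**4. Size, second set of assumptions.** True log10 level normal with SD 0.7 and site means 3.7 and 4.0 before truncation; measurement SD 0.2 at each visit; entry if the measured value is at least 3.0; the same true fall d in everyone; no intervention effect. The enrolled means are 3.92 and 4.12, a gap of 0.20.

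| d | Suppressed, 3.7 site | Suppressed, 4.0 site | Difference | Log10 DiD |
|---|---|---|---|---|
| 0 | 4.7% | 2.6% | +2.1 points | −0.008 |
| 0.5 | 27.1% | 17.8% | +9.3 points | −0.007 |
| 1.0 | 59.2% | 45.3% | +13.9 points | −0.007 |

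With the imbalance reversed (4.3 against 4.0) and d = 0.5, the result is 10.3% against 17.8%, a spurious deficit of 7.5 points. The bias can go either way.

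**5. Does adjustment repair it?** A logistic model with arm and baseline log10 viral load, averaged to a risk difference, was fitted to large simulated samples. Under step 3 the adjusted difference is about 0.1 point (d = 0.5 and 1.0). Under step 4 it is about 1.2 points at d = 0.5, against 9.3 crude. Some remains there because the measured baseline contains error.

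**The case against.** **The plan does not state a DiD for suppression.** Sections 2.1.1 and 2.12.4 place suppression at the 6-month assessment; section 2.15 writes the DiD on group means after naming only continuous outcomes; section 2.11.3 speaks of comparing changes without naming DiD. The model for a secondary binary outcome may also stand in an analysis plan that is not shown. This stands in part: only the general wording in sections 2.5 and 2.15 brings suppression under the rule. But that wording does cover it, and the article gives no other between-arm analysis of suppression.

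**Baseline viral load is rightly absent from the mixed model.** For log10 viral load it is already one of the two outcome measurements. This stands for the primary outcome. It does not help suppression, where the dichotomy drops the starting level.

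**Site confounding is conceded, and the bias is modest.** The Discussion says that site and intervention effects cannot be fully separated. At 60 per arm, 38.6% against 30.4% has a standard error of √(0.386×0.614/60 + 0.304×0.696/60) = 8.6 points, so the bias is about one standard error. That is fair. Yet the same section relies on adjustment for measured baseline differences, and this is a measured one.

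**Stronger readings that the documents do not support.** A reader might infer that the whole DiD analysis is empty; step 2 shows that the primary one is not. A reader might infer that many patients will become suppressed by measurement noise. With assumed within-person SD of 0.15 to 0.30 and no true change, this is 0.5% to 10% of all entrants; it cancels when the baselines match and leaves 2 to 3 points when the site means before truncation are 0.3 log10 apart (SD 0.2 to 0.3). Nor is starting level shown to be the main determinant of suppression: in step 3 the enrolled baseline SDs are 0.54 and 0.61 against a change SD of 1.0, so baseline explains 0.54²/(0.54² + 1) = 23% to 0.61²/(0.61² + 1) = 27% of endline variance.

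**Conclusion.** The point holds for the secondary suppression outcome only. Under the plan's general rule, its DiD equals the crude endline contrast of two hospitals and removes no difference in starting viral load. In the assumed scenarios with a shared fall of 0.5 log10, the spurious difference is about 8 to 9 points. Across the scenarios in steps 3 and 4 that favour the intervention site it runs from about 2 points (no fall) to 14 points (a fall of 1.0 log10), and an imbalance the other way changes its sign. The log10 DiD stays within 0.01 of zero throughout.

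Two conditions apply. The exact 0% requires that the qualifying viral load is also the baseline value. The documents do not settle this, but they mention no second entry measurement, and sections 2.11.3 and 2.12.1 take baseline viral load from records. The size rests on assumed distributions and an assumed site gap; if the sites start level, there is no bias from this source.

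**What to change.** State in section 2.15 that suppression is compared between arms at 6 months, not by DiD and not by the linear mixed model, using an adjusted risk difference or a logistic model that includes baseline log10 viral load. Keep the DiD for log10 viral load as it is, without adding baseline viral load as a covariate to that model. Reconcile the covariate lists in the Abstract and section 2.15 so that it is clear which list serves which outcome, with baseline viral load used for suppression. State whether the qualifying value serves as the baseline value.

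Baseline viral load is already collected (section 2.12.2.1), so only the wording of the analysis changes. The cost is one more covariate in a model of 120 patients. Adjustment does not remove other differences between the two hospitals, and the caution already given in the Discussion should remain.

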#### Baseline Survey

2.12.1

A baseline survey will be conducted prior to implementation of the intervention. Data will be collected through participant interviews and abstraction of clinical, laboratory, and patient medical records. Trained study nurses or research assistants will interview adult participants living with HIV–HBV co‐infection during enrollment using a structured questionnaire to collect socio‐demographic, clinical, behavioral, and HIV/HBV‐related information. Clinical and laboratory data, including HIV viral load, ART regimen, CD4 count, and other relevant medical information, will be extracted from participants' medical records and laboratory reports. In addition, Health Belief Model (HBM) constructs including perceived susceptibility, perceived severity, perceived benefits, perceived barriers, cues to action, and self‐efficacy as well as medication adherence and baseline knowledge regarding HIV–HBV co‐infection, will be assessed during the baseline evaluation.

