#### Follow‐Up and Endline Survey

2.12.2

Data will be collected at two time points: baseline (enrollment) and at the end of the 6‐month follow‐up period. At both assessment points, trained research nurses will collect socio‐demographic, clinical, and behavioral information through participant interviews and abstraction of medical records. Information on clinic attendance, retention in care, and pharmacy medication refill history among participants receiving ART will also be obtained from patient medical records. HIV viral load data will be collected at baseline and at the scheduled 6‐month follow‐up visit using laboratory viral load testing reports or dried blood spot (DBS) samples, where applicable. In addition, data on medication adherence, Health Belief Model (HBM) constructs, self‐management practices, and HIV–HBV‐related knowledge will be collected using structured questionnaires. All primary, secondary, and exploratory outcome measures will be assessed using data collected at these two time points to enable comparison of changes over time between the intervention and comparison groups.

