##### Patient Demographics and Treatment Variables

2.12.2.1

A structured data abstraction form and interviewer‐administered questionnaire will be used to collect participants' socio‐demographic, clinical, behavioral, and treatment‐related information under the supervision of the research team, which includes the principal investigator, a statistician, a clinical pharmacist, and senior medical experts. Trained research nurses will collect the data, while the principal investigator will oversee data quality through regular monitoring and validation.

Variables to be collected include age, sex, duration since HIV diagnosis, duration on ART, baseline and follow‐up HIV viral load, CD4 count, HBV serological status, comorbidities, concurrent medications, medication adherence, Health Belief Model (HBM) constructs, retention in care, and HIV–HBV‐related knowledge scores. These variables will be recorded at baseline and reassessed at the 6‐month follow‐up to evaluate changes over time and estimate the effect of the intervention.

Data will be obtained from participant interviews, patient medical records, laboratory reports, pharmacy refill records, and health facility electronic databases where available. All collected data will be anonymized by assigning unique study identification numbers before analysis to ensure participant confidentiality. Electronic datasets will be securely stored on password‐protected computers accessible only to authorized members of the research team.

Ethical approval will be obtained from the Institutional Review Board of the University of Gondar. Written informed consent will be obtained from all participants before enrollment. Permission to use standardized questionnaires and assessment tools will be secured from the respective developers or authorized sources prior to data collection.

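### Viral load before the qualifying value is neither a listed variable nor a covariate, so any difference between the two hospitals in passing versus persistent viraemia would bias the difference-in-differences

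*Protocol article*

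**What the plan says.** Section 2.6.1 of the protocol article admits adults with at least 6 months of routine follow-up who "have poor virological outcome (HIV viral load" of at least 1000 copies/mL). It mentions no repeat or confirming value. Section 2.12.2.1 lists "baseline and follow‐up HIV viral load, CD4 count, HBV serological status" among the variables and names no earlier viral load. Section 2.12.2 sets the schedule: "Data will be collected at two time points: baseline (enrollment) and at the end of the 6‐month follow‐up period".

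The sources are charts. Section 2.12.1 covers "Clinical and laboratory data, including HIV viral load, ART regimen, CD4 count, and other relevant medical information", which "will be extracted from participants' medical records and laboratory reports". Section 2.12.4 adds that further clinical information bearing on virological outcomes will be taken from the same records.

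Section 2.10.1 evaluates the primary outcome by "comparing the mean change in log‐transformed viral load between the intervention and comparison groups". Under section 2.8 each arm is one purposively assigned hospital, and participants are randomly sampled from that hospital's own eligible patients.

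There are two covariate lists. The Abstract names age, sex, education, baseline viral load, ART duration and adherence. Section 2.15 names twelve covariates, including treatment interruption, for a random-intercept model with group, time and their interaction. It mentions no covariate-by-time terms. Neither list contains viral load history.

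**The concern.** A patient whose previous value was below 1000 and a patient with repeated values above it can be expected to change differently over 6 months, with or without education. Random sampling within a hospital reproduces that hospital's mix of the two. Differencing removes stable differences in level between hospitals. It does not remove differences in expected change, and that is where these two kinds of patient differ.

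If the intervention hospital has more passing elevations, education looks better than it is. If it has fewer, a real effect is masked. Section 2.15 intends the estimates to inform the design and size of later studies, so a distorted effect would carry forward. History is also a likely strong predictor of change, so leaving it out costs some precision.

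**Working it through.** **The plan's own figures (section 2.7).** n = 2 × 15² × (1.96 + 0.84)² / 8.4² = 3528 / 70.56 = 50 per group, which reproduces. The plan enrols 60 per group and expects 20% loss: 60 × 0.80 = 48 completers per arm. The design effect is 8.4 / 15 = 0.56 SD.

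**Assumptions not in the documents.** Without education, passing elevations fall 1.5 log10 in 6 months and persistent ones 0.3, a gap of 1.2. The SD of change is 1.0 log10. The hospitals differ by 10, 20 or 30 percentage points in the share of passing elevations.

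**Bias and type I error.** Bias = difference in share × 1.2. SE = 1.0 × √(2/48) = 0.204. Type I error = P(|Z + bias/SE| > 1.96).

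| Difference in share | Bias (log10) | Bias / SE | Type I error |
|---|---|---|---|
| 10 points | 0.12 | 0.59 | about 9% |
| 20 points | 0.24 | 1.18 | about 22% |
| 30 points | 0.36 | 1.76 | about 42% |

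At an SD of 1.0 the design effect is 0.56 log10, so the 20-point bias is 0.24 / 0.56 = 43% of it.

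**Check by simulation.** No true effect, 48 per arm, 3000 runs per scenario, residual SD 0.7, endline floored at 1.3 log10. Passing elevations fall 1.5 or 2.0 log10 and persistent ones 0.5. Mean baseline is either 3.5 (passing) and 4.3 (persistent), or 3.9 in both.

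| Difference in share | False effect, change scores | Type I error | False effect after baseline adjustment |
|---|---|---|---|
| 10 points | 0.09 to 0.14 | 9 to 12% | 0.07 to 0.14 |
| 20 points | 0.18 to 0.28 | 20 to 31% | 0.15 to 0.28 |
| 30 points | 0.28 to 0.41 | 40 to 58% | 0.22 to 0.41 |

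Adjusting for baseline viral load, as the Abstract proposes, removed between none and about a fifth of the bias. Adding a perfectly measured passing/persistent indicator brought the bias to about 0 and the type I error to about 5%.

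**What the section 2.15 model does.** With two time points and complete data, the group-by-time coefficient is the between-group contrast of within-person changes. A covariate that is constant over time and enters only as a main effect cannot alter that contrast. In one simulated data set the estimate was -0.133 both without the type indicator and with it as a main effect. It moved only when the indicator's time interaction was added.

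**Precision.** With a 50:50 mix, the variance between types is 1.2² × 0.25 = 0.36. Perfect classification would leave an SD of √(1 - 0.36) = 0.8 and an SE of 0.163. If the chart class is right 80% of the time in each direction (assumed), the gap between classes is 1.2 × (0.8 - 0.2) = 0.72 and the explained variance is 0.72² × 0.25 = 0.13. The residual SD is then √0.87 = 0.93 and the SE is 0.93 × 0.204 = 0.19.

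**The case against.** A reader might infer that earlier viral loads will not be collected. The article does not establish that. Its list opens with "Variables to be collected include age, sex, duration since HIV diagnosis, duration on ART", which is not closed wording, and sections 2.12.1 and 2.12.4 both leave room for further chart information. The two time points are the assessment schedule, not a limit on history. A reader might also infer that the plan declares one value sufficient. Section 2.6.1 only gives a threshold and is silent on confirmation.

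Treatment interruption (section 2.15) and adherence (Abstract) are related to persistence and may act as partial proxies. The Discussion already concedes residual confounding from unmeasured participant or facility factors, and section 4 concedes that adherence-related and resistance-related failure cannot be told apart. Section 2.15 puts magnitude and precision ahead of significance. Nothing in the article suggests that the hospitals differ in this mix, and the falls, the SD and the imbalance are all assumed.

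Most of this stands, and it limits the claim. Three things remain. No list that the article does give, whether of variables or covariates, names earlier viral load. As baseline main effects in the section 2.15 model, the proxies would leave the group-by-time estimate unchanged with complete data. And the conceded confounding is of unmeasured factors, whereas earlier viral load is probably in the charts of many of these patients.

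**Conclusion.** The point holds as a conditional weakness that is cheap to reduce. If the hospitals differ in their mix of passing and persistent viraemia, the primary contrast absorbs the difference, and the adjustment described does little or nothing about it. The size is 0.12, 0.24 or 0.36 log10 for 10, 20 or 30 points, with type I error of about 9%, 22% or 42%. These figures rest on an assumed 1.2 log10 gap, an SD of 1.0 and 48 completers per arm.

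A reader might go further and conclude that the result will be biased, or that recording history would cure it. Neither follows. The existence and direction of a hospital difference are unknown. One earlier value below 1000 may precede either a passing elevation or newly started persistent failure, so classification is imperfect. An SE of 0.163 would need perfect classification; about 0.19 is the example at 80% accuracy.

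**What to change.** At both hospitals, abstract the last viral load before the qualifying one, with its date. If the full protocol or abstraction form already provides for this, say so. Classify each participant as earlier value at least 1000, earlier value below 1000, or no earlier value, and show the class by hospital in the baseline table.

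Prespecify an adjusted or sensitivity analysis of the primary outcome that includes the class and its interaction with time, or equivalently the class as a covariate in a model of change. A main effect alone would not serve. Eligibility and care do not change, and the item can be abstracted retrospectively.

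The cost is one dated chart item for 120 patients and a few parameters. A three-level class adds four (two main effects and two interactions) in the mixed model, or two in a model of change. With about 96 completers and twelve covariates already named, weakly justified ones may need to be dropped. Some patients will have no earlier value, and misclassification will leave part of the bias in place.
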